### Data safety and management

The Lucy app prioritizes the data security and anonymity of its users. It employs robust encryption measures to safeguard all data. Without the user’s password, it is technically impossible to decrypt any stored information. Furthermore, even in the unlikely event of decryption, it is essential to note that our servers do not store personal identifier information. This ensures an additional layer of protection for user privacy and data security.

The app does not ask for personal data (e.g., name, date of birth, e-mail address, etc.) from the user, and registration is not needed to use it; moreover, the IP address is not displayed and stored. The questionnaire by itself does not permit the direct identification of an individual and does not contain other information that, when combined, allows a particular individual to be indirectly identified. Accordingly, indirect identifiability is possible when data is combined with additional information that distinguishes and allows for the identification of an individual.

The free text fields within the application are securely encrypted on the servers, ensuring they remain protected. These fields are only decrypted and displayed in an unencrypted format on the user’s device. This approach allows the data to be utilized for research purposes while maintaining the utmost privacy and preventing any possibility of personal identification.

## Ethics and dissemination

All individuals must approve the privacy policy and informational disclosure, explicitly stating that their data may be used for research purposes in the *Lucy app* before participation (see Supplementary Data for Informed Consent Form). The non-interventional study protocol was approved by the ethics committee of the Medical Research Council of Hungary and authorized by the National Institute of Pharmacy and Nutrition of Hungary (OGYÉI/31355/2021) concerning scientific content and compliance with applicable research and human regulations. It is conducted following the tenets of the Declaration of Helsinki. Any modifications to the protocol will be notified and reviewed by both research ethics committees following regulations for research in the respective country. Results will be presented at national or international conferences and published in international high-impact, peer-reviewed journals.

## Conclusions

Endometriosis affects up to 190 million women worldwide and remains unresolved mainly in terms of etiology and optimal treatment strategy. It is often associated with chronic pelvic pain, infertility, and reduced quality of life. Despite this high prevalence, recognition of the disease is inadequate, underprioritized, and research is underfunded, contributing to diagnostic delays of 4 to 11 years. Therefore, the present study investigates the association between self-reported data and clinical presentation of endometriosis and aims to develop a phenotypic description of women with endometriosis. Using a big data approach, the data collected will be linked to existing registry-based information on endometriosis diagnosis and health care utilization. By unraveling the etiological aspects, we could identify patterns that may lead to categorizing novel clinical subgroups within the disease. This could enable earlier detection of endometriosis, thereby reducing current diagnostic delays. In addition, our study aims to identify different dietary components that may worsen the quality of life and pain in women with endometriosis, upon which we can make real-world data-driven nutritional recommendations. Ultimately, the findings from this multifaceted study have the potential to reduce diagnostic delays, improve patient care, and pave the way for more personalized and targeted approaches to managing endometriosis, marking a pivotal step toward enhancing the overall well-being of affected individuals.

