## Introduction

Endometriosis is a chronic inflammatory disease with endometrium-like tissue outside the uterine cavity [1, 2]. It is commonly associated with chronic pelvic pain, infertility, and decreased quality of life, although asymptomatic cases exist [3–5]. The exact prevalence of endometriosis is unknown, but it may affect 5–10% of women and those assigned female at birth during their reproductive years, which equals nearly 190 million people worldwide [1]. Despite this high prevalence, recognition of the disease is inadequate, underprioritized, and research is underfunded, contributing to diagnostic delays ranging from 4 to 11 years [6–9]. Accordingly, endometriosis should be considered a public health issue, and reducing the current diagnostic delay is paramount.

Lucy is a mobile health application (Lucy app) designed to alert users with an increased risk of endometriosis to seek medical attention. Users can input their menstrual cycle information, health status, medical records or diagnoses, dietary details, lifestyle, and pain symptoms. Specialists in reproductive gynecology and health psychologists developed the app’s algorithm to continuously analyze the recorded data and alert the user when the entered symptoms are strongly associated with endometriosis.

A baseline questionnaire and a longitudinal questionnaire were developed and implemented as an additional module in the Lucy app. It collects self-reported data on symptoms of endometriosis, socio-demographics, mental and physical health, economic factors, nutrition, and other lifestyle factors [10]. By linking the collected information with existing registry-based information on diagnoses of endometriosis, healthcare use, and the big data approach, we can develop a phenotype description of individuals with endometriosis and structured clinical data [11].

So far, only one study has investigated this question with big data analysis using machine learning (ML). According to Bendifallah *et al*., endometriosis can generally be diagnosed with high diagnostic accuracy based on endometriosis-related symptoms and demographic data using ML technology [12]. The work presented by these authors was based on medical records of 800 participants of a French cohort and not on patient self-reported data.

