## Materials and methods

### Ethics statement

This non-interventional study protocol was approved by the ethics committee of the Medical Research Council of Hungary and authorized by the National Institute of Pharmacy and Nutrition of Hungary (OGYÉI/31355/2021). It is conducted following the tenets of the Declaration of Helsinki. Before completing the questionnaires for the first time, participants will receive an informational briefing detailing the nature of the research. The application necessitates accepting the privacy policy and informational disclosure, explicitly stating that their data may be used for research purposes. The data controller only stores aggregated, anonymous data from the data provided in the *Lucy app* and the use of the application. See https://hellolucy.app/hu/protection and https://hellolucy.app/hu/agreement for detailed information.

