### Eligibility criteria

5,000 women with confirmed endometriosis and 5,000 women without diagnosed endometriosis in a control group aged 18–45 years will be enrolled and followed up for one year.

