### Questionnaire

Participants will be asked to complete a baseline questionnaire once and a longitudinal questionnaire monthly for one year. The questionnaire includes questions about endometriosis symptoms, socio-demographic information, mental and physical health, known medical conditions, medication use, dietary habits, economic burden, and lifestyle factors. These include free-text responses, single or multiple-choice questions, and numerical rating scales. See Supplementary Data for the questionnaires and https://hellolucy.app/en/ for the Lucy app.

Self-reported data of the participants will be measured as follows:

Evaluating the quality of life using the 5-level EQ-5D (EQ-5D-5L) and Endometriosis Health Profile 5 (EHP-5) [18].Assessing pain scores using the Visual Analogue Scale (VAS) [19].Examining somatic and emotional symptoms associated with central pain sensitization using the short version of the Central Sensitization Inventory (CSI-9) [20].

If using the same user account, Lucy app users can pause and resume completing the questionnaire, even on different devices. Once all questions have been answered, users can review and modify their answers on a summary screen. When they submit the questionnaire, their responses are stored on a server. At this point, the questionnaire’s content is fixed and cannot be changed.

In longitudinal studies, minimizing the drop-out rate and encouraging maximum user participation in completing the desired quantity of questionnaires is crucial. *Lucy app* users are anonymous; therefore, personal email contact is impossible. To address this challenge and reduce dropouts, the application uses several methods to notify users when the questionnaire becomes available for completion again. The questionnaire menu is prominently displayed on the application’s main page, and a pop-up window alerts users that the questionnaire is complete. Users can track the number of times and when they completed the questionnaire, but detailed completion data is not visible. The app displays a pop-up window with motivational quotes and positive messages to encourage and support users. In addition, users who complete the questionnaire are entered into a drawing as an additional incentive to participate. These measures are designed to minimize dropout and maximize user engagement in completing the questionnaires for the study.

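### The article promises registry linkage to describe individuals, but the anonymous, aggregated data it describes do not allow person-level linkage or verification of a participant's diagnosis

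*Protocol article*

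**What the plan says.** Linkage is claimed in three places in the protocol article. The Conclusions state without condition that "the data collected will be linked to existing registry-based information on endometriosis diagnosis and health care utilization". The Introduction makes linkage the route to the phenotype: "By linking the collected information with existing registry-based information on diagnoses of endometriosis, healthcare use, and the big data approach", it says, "we can develop a phenotype description of individuals with endometriosis and structured clinical data". The concluding paragraph of the Abstract makes the same claim.

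Three sections describe the data differently.

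- Ethics statement: "The data controller only stores aggregated, anonymous data".
- Questionnaire: users are anonymous, which is given as the reason why they cannot be contacted by e-mail.
- Data safety and management: "our servers do not store personal identifier information". The app asks for no name, birth date or e-mail address and does not keep the IP address. The questionnaire is said to hold nothing that would identify a woman even in combination.

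The Eligibility criteria plan for "5,000 women with confirmed endometriosis" and an equal number of women without a diagnosis. The Abstract and the Questionnaire section describe the information as self-reported, and according to the Introduction users enter their own diagnoses or records.

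The Questionnaire section asks for one baseline and monthly follow-up questionnaires for a year. The Statistical and machine learning analyses section plans LSTM models on the resulting time series.

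**The concern.** Linking a person's app record to a registry record needs something common to both: a direct identifier, a set of quasi-identifiers, or a key created with consent. The article says that the first two are absent and does not mention the third. The promise and the data description cannot both be true as written.

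Two things are at stake. First, readers would take the phenotype to rest partly on registry diagnoses and recorded healthcare use, when on the description given it rests on what women enter in an app. The diagnosed or undiagnosed label is what the Random Forest and LSTM risk models must learn from, so how it was obtained bears directly on what the primary objective can conclude. Second, the anonymity statements are assurances to participants, and carrying out the linkage would contradict them.

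Separately, if only aggregates were kept, there would be no series per woman to follow for a year or to feed to a sequence model.

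**Working it through.** The article gives no figure on this point, so there is nothing to reproduce. The check sets the sections side by side.

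**1. Is the promised linkage at person level?** The Introduction's product is a description of individuals with endometriosis. Comparing app totals with registry totals would not give that, and it would not check any one woman's diagnosis. The natural reading is person-level linkage.

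**2. Do the data described allow it?**

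| What linkage could use | What the article says |
|---|---|
| Direct identifier | Not requested by the app, not held on the servers (Data safety and management) |
| Combination of questionnaire items | Said not to identify a woman (same section) |
| Contact with the participant to obtain a key | Users anonymous, e-mail contact impossible (Questionnaire) |
| In-app user account | Joins sessions within the app ("If using the same user account, Lucy app users can pause and resume"), but is not a registry key |
| Consented linkage key, named registry | Not mentioned in the shown text |

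One sentence points the other way. Directly after ruling out indirect identification, Data safety and management says it is possible with additional information. This contradicts the sentence before it, and it names neither the information nor a procedure. It is a further item to reconcile and does not describe a linkage route.

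**3. Can a diagnosis be verified independently?** The routes would be a registry, a medical record tied to the woman, or contacting her again. The first fails by step 2. For the second, users may enter records themselves, but no check of them is described. For the third, e-mail contact is ruled out. As described, the label is the woman's own report, possibly of a diagnosis that was itself well confirmed.

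**4. Does aggregated storage fit the analyses?** The Questionnaire section has each user's submitted responses stored on a server, lets users see how often and when they completed it, and repeats it monthly for a year. The LSTM models use the temporal progression of symptoms. All of this needs user-level records. The Ethics statement says that only aggregated data are stored. One of the two descriptions is wrong, and the weight of the text suggests that it is the word *aggregated*.

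**5. What depends on the linkage?** The primary objective does not mention it, and no method in the Statistical and machine learning analyses section uses it. Removing the claim would leave every stated analysis in place. What changes is how the data source and case status may be described.

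**The case against.** The strongest reply is that the contradiction touches little of the plan. Linkage appears only in framing sections, the article says openly that its data are self-reported, and the supplementary questionnaire and consent form, which may settle some of this, are not shown. That argument limits the point but does not remove it: the conflicting statements all stand in the shown text, and the Conclusions say without qualification that linkage will happen.

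It does dispose of several stronger readings that a reader might infer:

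- *The reference standard is misstated.* The article never names a registry as its reference standard and never says that confirmation comes from one.
- *The word confirmed is false.* It can mean that the woman reports a confirmed diagnosis. How this is asked belongs to the questionnaire.
- *One woman may be counted several times, because registration is not needed while continuity runs through an account.* Registration-free use and a pseudonymous account can coexist. The text mentions a user password and does not say that the questionnaire works without an account.
- *Free text is promised for research but cannot be read.* The fields are encrypted on the servers ("These fields are only decrypted and displayed in an unencrypted format on" the user's device), but the next sentence speaks of the data in general, and it is unclear whether that includes the free text.
- *The LSTM models are infeasible.* Loose wording for pooled user-level data is the likelier explanation, and a correction of wording would suffice.

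It could also be said that linkage means comparison with registry totals. Anonymous data would allow that, but it does not fit the Introduction's description of individuals.

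**Conclusion.** The point holds in a limited form. The article promises a property, linkage to registry diagnoses and healthcare use in order to describe individuals, that the data it describes cannot deliver. Independent verification of a participant's diagnosis is likewise not possible as described. Aggregated-only storage conflicts with the planned follow-up and sequence models.

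This should be fixed, but it does not undermine the stated analyses, none of which uses linkage. No numerical size is given: the documents hold no rate of false or missed self-reported diagnoses, and any figure would only restate an assumption. The conclusion rests on reading linkage as person-level and on no consented key being set out in the unseen consent form or supplement. If such a key exists, the remedy is to describe it and to correct the anonymity statements.

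**What to change.** Reconcile the sections as follows.

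1. Withdraw the registry-linkage claim from the Abstract, Introduction and Conclusions, or limit it to comparison with registry totals. Keep person-level linkage only if a consented key already exists, and then describe the key and the registries.
2. Correct *aggregated* in the Ethics statement to match the user-level records that the follow-up and models need. Settle the two conflicting sentences on indirect identification in Data safety and management.
3. Describe the groups as self-reported diagnosed and self-reported undiagnosed, unless a verification step exists and is stated.
4. Where the questionnaire records how the diagnosis was made, repeat the main classification model by reported basis of diagnosis as a sensitivity analysis.

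The cost is changes of wording, a modest extra analysis, and a weaker but accurate claim. A new linkage key or a mandatory account identifier is not recommended here. Recruitment began in February 2022 and users cannot be e-mailed, so neither could easily be added for women already enrolled, and the shown text does not establish what the app already stores per user.
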